# Effects of prebiotics on microbial diversity and abundance in young children with acute malnutrition: study protocol for a multi-centered, double-blinded randomized controlled trial

**DOI:** 10.1186/s13063-024-08647-z

**Published:** 2024-11-26

**Keywords:** RUTF, Prebiotics, SAM, Gut microbiome

## Abstract

**Background:**

The anti-inflammatory and antimicrobial benefits of prebiotics may present an affordable and cost-effective strategy for not only the prevention but also treatment of malnutrition. Therefore, the present trial has been designed with the aim to evaluate the role of prebiotics on the gut microbiome of severe acute malnourished (SAM) children.

**Methods:**

The study is designed as a prospective, double-blinded, triple-armed, multi-centered randomized controlled trial, with 6–59 months old uncomplicated SAM children recruited to the experimental group receiving ready-to-use therapeutic food (RUTF) plus prebiotics and the active comparator group receiving RUTF plus starch for 2 months duration (8 weeks). Healthy children with matching age and gender will be recruited to placebo comparator group and will receive starch as a placebo during the study period. A total of 58 participants will be recruited to each arm with 1:1:1 allocation ratio following a pre-defined inclusion and exclusion criteria. The results of the gut microbiome diversity will serve as the primary outcome, while weight-for-height/length *z*-score, mid-upper-arm circumference, neurodevelopment assessment, and body mass accumulation will serve as the secondary outcome. Data collection and evaluations will be conducted at baseline and at the end of the trial (week 8), while the safety monitoring will be conducted at every second week. For analysis, the principles of intention-to-treat will be followed.

**Conclusions:**

Conclusively, the results of the present trial would provide useful insights and high-quality data for the treatment and management of SAM children by evaluating the effect of RUTF plus prebiotic on the gut microbiome diversity of children, leading to medical evidence for designing the large-scale studies.

**Trial registration:**

The present trial is registered at ClinicalTrials.gov with identifier No: NCT06155474 and registration date 4 December 2023.

## Background

Malnutrition is a major global public health concern with its outcomes linked to poor health and early morbidities among children under five, particularly in developing countries. Pakistan reported to have one of the highest prevalence of malnutrition among children in comparison to other developing countries [1]. About 45% of children are projected to be stunted, 10.5% wasted, and 31.6% underweight [2]. In 2021, 5 million children died worldwide due to infectious diseases or malnutrition, with Pakistan having the highest under-five mortality rate [3]. With a population of approximately 229 million, Pakistan is reported to be the fifth most populous country in the world. The under-five mortality in the country has reported to be 63.3 per 1000 live births in 2021 [3, 4]. Although mortality and malnutrition are often attributed to infections among under-five children, latest research highlights the presence of immature gut microbiome among malnourished children [5–9].

Gut microbiome are distinct microbial communities where trillions of different microscopic organisms including viruses, bacteria, and fungi live [10]. These microscopic organisms play a significant part in strengthening the gut integrity [11], regulating immunity [12], protecting against pathogens [13], harvesting energy [14], and influencing functions beyond the gut [10]. Nevertheless, the impairments in gut microbiome can be triggered by various environmental and subclinical characteristics that could lead to reduced intelligence quotient, growth faltering, and severely acute malnutrition (SAM) among children [9, 15–17].

With persistence iron and B_12_ deficiency and symptoms of diarrhea, pneumonia, acute gastroenteritis, and acute respiratory infections among SAM children [18], ready-to-use therapeutic food (RUTF) has proven to be a revolutionary rehabilitative therapy. The therapy of RUTF is used for managing the malnutrition among children by promoting weight gain and improving developmental potential [19, 20]. However, iron present in standard RUTF may not be sufficient to elevate circulating levels of ferritin into the optimal physiological range as one meta-analysis revealed higher hemoglobin levels and lower rates of anemia among SAM children when treated with high iron content as compared to standard RUTF [21]. The rate of relapse has also been a question among children treated with RUTF.

With deficiency of iron recognized in malnourished children [18], galactooligosaccharides (GOS), a form of prebiotic, have been proven to have anti-inflammatory and antimicrobial actions that might enhance response to standard therapy for SAM [22, 23]. These benefits have developed a rising interest in the use of prebiotics in diet to adjust gut microbiome in a way that can improve microbial health [24]. Targeting the gut microbiota through the use of prebiotics as a part of treatment in malnourished children may present an affordable and cost-effective strategy for the prevention and treatment of malnutrition among children as well as in improving their overall health [22]. Prebiotics are considered as a fuel for probiotics bacteria of gut that could protect the host against diarrhea with reduced rates of relapse. However, randomized controlled trials evaluating the effects of prebiotic supplementation on the gut microbiome among children with SAM have not previously been studied. So, there is a gap, as clinical evidence is lacking and the existing knowledge cannot be translated into clinical practice.

Around one trillion organisms per milliliter of luminal contents are found in the distal intestine, where the majority of these bacteria are found [10]. It is essential to describe the microbiota in malnourished children in order to define their potential to harvest energy and nutrients [25]. Therefore, the present study has been designed with the goal to evaluate the effect of prebiotics on the gut microbiome diversity in malnutrition children utilizing a prospective, double-blinded, triple-armed, multi-centered randomized controlled trial. The specific objectives of the present study are to:Examine the role of prebiotics on the microbiome diversity and abundance among malnourished children using 16 Svedberg (S) ribosomal ribonucleic acid gene sequencingInvestigate the role of prebiotics on the anthropometric measures and the body composition of malnourished childrenAssess the impact of prebiotic supplementation on malnourished children’s neurodevelopment

## Methods

### Trial design

The present trial is designed as a prospective, double-blinded, triple-armed, multi-centered randomized controlled trial. The trial will be conducted following the guidelines Declaration of Helsinki, Standard Protocol Items: Recommendations for Interventional Trials (SPIRIT) [26], and Consolidated Standards of Reporting Trials (CONSORT) [27]. The trial design has been approved by the Institutional Ethics Review Board (IERB) (Letter No. D/137/FIMS) and is registered under the Clinical Trial Registry at www.clinicaltrials.gov with study ID NCT06155474. The flow diagram of the trail design is illustrated in Fig. 1.

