### Randomization and allocation

Children suffering from acute malnutrition, otherwise healthy, aged 6–59 months, and fulfilling the inclusion criteria will be recruited randomly to one of the two arms of the present trial for 8 weeks, i.e., experimental and active comparator groups. However, healthy children with matched sex and age will be recruited from the vaccination centers of the research sites to the placebo comparator group as healthy controls. The participants in all groups will be recruited in equal allocation ratio (1:1:1) with no restriction of block size. A statistician unaware of the study method will generate the random numbers and allocate the participants to study groups by assigning unique code to them (i.e., SAM children to experimental and active comparator group and healthy children to placebo comparator group). All the participants will be given a recruitment card with their unique identity code mentioned on it.

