### Blinding

A statistician unaware of the study, responsible for designating codes to the participants and allocation of groups, will prepare the packets of treatment regime for all the participants with day-wise dosage enclosed in separate opaque envelops and the unique code of the participants mentioned on it, blinding the participants and the investigator of the study. The treatment to all the participants will be given in separate rooms, and the parents of all the participants will be advised not to acquainted and communicate with each other after randomization for reducing the subjective biases. Blinding will only be permissible in case of withdrawal or termination of any study participants.

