### Interventions

The detailed dietary intervention that will be provided to the participants recruited to each group is given in Table 2.

**Table 2 Tab2:** Intervention for study groups

*Participant group/arm*	*Intervention/treatment*
Placebo comparator: healthy controls (starch) The healthy controls will be given starch packed in the same way as the active prebiotics	**Dietary supplement: starch only** The starch solution is a low-fat diet **Dosage:** A daily dosage of 4 g of starch mixed with water or milk
Experimental: malnutrition (RUTF plus prebiotics) The malnutrition group with RUTF and prebiotic only. The RUTF will be given as per the WHO guidelines	**Dietary supplement: prebiotic galactooligosaccharide (GOS) Powder** Prebiotic GOS powder is a galactooligosaccharide ingredient low in mono-sugars. Scientific studies have shown positive effects of oligosaccharides, among which GOS, on growth of bifidobacterial, stool consistency bowel function and transit time, support of natural defenses and mineral absorption The product mainly consists of 97% dry matter with 69% prebiotic GOS, 23% lactose, and 5% glucose and galactose as monosaccharides. These prebiotics have β-(4) glycosidic linkages and have been proven as safe product **Dosage:** In this arm, participants will receive a daily dosage of 4 g of prebiotic GOS mixed with milk or water along with RUTF. The dosage of RUTF will be determined based on the weight of the child in such a way that two sachets will be given to a child with a weight of 5–6.9 kg in a day/week, three sachets to a child weighting 7–9.9 kg in a day/week, and four sachets were given to a child with having weight less than or equal to 10 kg in a day/week
Active comparator: malnutrition (RUTF plus starch) The malnutrition group with RUTF and starch only. The RUTF will be given as per the WHO guidelines	**Dietary supplement: RUTF plus starch** RUTF and the starch solution **Dosage:** In this intervention arm of the trial, participants will receive a daily dose of 4 g of starch mixed with milk or water along with RUTF. The dosage of RUTF will be determined based on the weight of the child in such a way that two sachets will be given to a child with a weight of 5–6.9 kg in a day/week, three sachets to a child weighting 7–9.9 kg in a day/week, and four sachets were given to a child with having weight less than or equal to 10 kg in a day/week

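### Double-blinding is claimed for all three arms, but the healthy arm is set by health status and gets no RUTF, so both SAM-healthy contrasts are open and non-randomised

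*Protocol article*

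**What the plan says.** The Trial design section calls the study "designed as a prospective, double-blinded, triple-armed, multi-centered randomized controlled trial". The title, the abstract and the end of the Background also claim double-blinding, and none of these places limits it to particular arms.

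The Blinding section gives the mechanism. A statistician "will prepare the packets of treatment regime for all the participants", with each day's dose "enclosed in separate opaque envelops and the unique code of the participants mentioned on it, blinding the participants and the investigator of the study".

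The Randomization and allocation section describes two routes into the trial. Children with SAM "will be recruited randomly to one of the two arms of the present trial for 8 weeks, i.e., experimental and active comparator groups". For the third group, "healthy children with matched sex and age will be recruited from the vaccination centers of the research sites to the placebo comparator group".

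Table 2 gives both SAM arms 4 g of powder a day with RUTF, and gives the healthy arm 4 g of starch a day without RUTF. It labels the healthy arm the placebo comparator.

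The Outcome parameters section makes comparison with healthy children part of the primary outcome. It describes the assessors as separate from enrolment and allocation, but does not say they are blinded. The Statistical analysis section compares outcomes across the three groups by ANOVA with post hoc tests, or by Kruskal-Wallis.

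**The concern.** A double-blind label tells readers that neither the family nor the people measuring outcomes knew the child's group. Coded packets can hide which powder a child receives. They cannot hide whether the child was enrolled as malnourished or healthy, or whether the family is also given RUTF. In the third arm these two facts are the group assignment.

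What is at stake is how the SAM-healthy contrasts are read. The Malawi Development Assessment Tool, length, MUAC and body composition all depend on staff who measure or score. A difference between SAM and healthy children on these outcomes is measured with group known, and it compares groups that were not formed by randomisation. If such a difference is reported under a double-blinded, randomised label, it is credited with protection against observer bias and confounding that it does not have.

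**Working it through.** No figure in the article depends on blinding, so the check sets sections side by side and counts the children and contrasts affected.

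1. **The plan's own sample size.** The Sample size estimation section gives 53 per group for a one-way ANOVA with k = 3, f = 0.25, 5% significance and 80% power. With noncentrality k × n × f², power is 0.797 at n = 52 and 0.805 at n = 53, so 53 is reproduced. The recruitment target is 58 per arm, and 3 × 58 = 174. The point below changes none of these numbers.

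2. **Scope of the claim.** Trial design covers three arms without restriction. Blinding covers packets for all participants and names both participants and the investigator as blinded. The claim therefore includes the healthy arm.

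3. **How a child enters the third arm.** Under Randomization and allocation, chance decides only between the two SAM arms. Health status alone puts a child in the third, so anyone who knows that status knows the arm.

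4. **What the family receives.** Under Table 2, both SAM arms get RUTF and the healthy arm does not. Whether RUTF is handed out also reveals the arm, even to someone who has not seen the child. No assumption about how the children look is needed.

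5. **Who can still be masked.**
   - Parents and investigators: not masked to SAM versus healthy, by steps 3 and 4.
   - Staff measuring neurodevelopment, anthropometry and body composition: being separate from enrolment and allocation does not hide health status. At baseline, MUAC and weight-for-height are themselves SAM entry criteria (Table 1), so the measurement usually shows the group.
   - Laboratory: stool samples carry the allocated codes (Data collection), so sequencing can be masked.
   - Statistician: stated to be blinded (Statistical analysis), which coded group labels can support.

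6. **Extent.** Children: 58 / 174 = 33%. Three groups give 3 pairwise contrasts: GOS versus starch within SAM, GOS versus healthy, and starch versus healthy. The last two include the healthy arm, so 2 of 3 are open and non-randomised. The remaining one is the randomised comparison.

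**The case against.** The strongest reply is that this is a matter of labelling. The article says openly that only two arms are randomised and calls the third group healthy controls, so a careful reader is not misled. The objectives concern the effect of prebiotics in malnourished children, which is the randomised comparison. The primary outcome comes from sequencing coded stool, with a blinded statistician. Staff could not be blinded to health status in any design with a healthy group.

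Much of this stands. The effect on the sequencing outcome is small, and no calculation changes. But the blinding statement is still wrong as written for one arm, and the healthy comparison is not incidental: it is part of the stated primary outcome and of the three-group tests. That such blinding is impossible is a reason not to claim it.

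A reader might go further and infer that the blind also fails between the two SAM arms, because the match is in packing only or because taste gives the product away. The documents do not support this.
- The sentence "The healthy controls will be given starch packed in the same way as the active prebiotics" is in the healthy-control row and does not define the match between the SAM arms. Those arms also share the daily amount, the milk or water vehicle, RUTF and coded opaque envelopes.
- The GOS powder contains "23% lactose, and 5% glucose and galactose as monosaccharides", which is 4 g × 23% = 0.92 g plus 4 g × 5% = 0.20 g, or 1.12 g of sugars per dose. The article gives no composition for the starch and no evidence that the difference can be tasted. A condensed article may leave sensory matching to the full protocol.

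Nor do the healthy children come from another clinic: the vaccination centers belong to the research sites. The article promises no survey of treatment guesses, so the lack of one contradicts nothing.

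**Conclusion.** The concern holds for the healthy arm only. The article claims double-blinding for all three arms, but its allocation rule and Table 2 make that impossible for SAM versus healthy at the level of parents, investigators and outcome assessors. The extent is 58 of 174 children and two of three pairwise contrasts. Within that, the assessor-measured outcomes are the exposed ones. Coded stool sequencing and the statistician can remain masked, so the primary outcome is little affected.

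Two assumptions remain. The participant codes must not themselves show the group; otherwise the masking of laboratory and statistician is lost too. And no undisclosed arrangement keeps week 8 assessors from learning a child's status or regimen; the article describes none.

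Nothing here shows that the blind between RUTF plus GOS and RUTF plus starch is inadequate. No sample size or power figure changes.

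**What to change.** - In the title, abstract, Background, Trial design and Blinding text, limit double-blind and randomised to the comparison of RUTF plus GOS with RUTF plus starch.
- Replace the placebo comparator label with a non-randomised, unblinded healthy reference group.
- In the Outcome parameters and Statistical analysis sections, and in the results report, present SAM-healthy differences from the three-group analysis as open, observational comparisons. State that for these contrasts only the coded stool sequencing and the statistician can remain masked.

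The cost is wording and the notification that the Protocol amendments section already requires. Sample size, treatments and visits do not change. Expected recruitment was to close on July 31, 2024, so if those dates held, the correction can still be made in the analysis documents and the results report. The price is a less favourable but accurate blinding claim.

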**Fig. 1 Fig1:**
[figure not shown]
CONSORT flowchart

### Study setting

The trial will be conducted at two public sector District Health Quarter (DHQ) level hospitals in Lahore, i.e., Government Mian Mir DHQ and Government Samnabad DHQ. Permissions will be taken from the relevant authorities of the hospitals. These two hospitals are selected as currently Integrated Reproductive Maternal Newborn, Child Health (IRMNCH) & Nutrition Programs are running in these hospitals with a high patient load.

### Study population and eligibility criteria

All children suffering from SAM, without any complications, and aged 6–59 months, are eligible for inclusion in the present trial. Participants will be screened using weight-for-height/length *z*-score and mid-upper arm circumference (MUAC) as screening criteria. The criteria of the World Health Organization (WHO) will be used to diagnose edema among children. WHO defines children with grade 1–2 bilateral edema and a weight-for-height/length *z*-score of < − 3 standard deviations (SD) or MUAC of < 11.5 cm who are otherwise clinically healthy, aware, and with a decent appetite as children with SAM [28]. Trained healthcare staff including nurse, childcare worker, and doctor will assess the children for eligibility. MUAC will be assessed using WHO’s MUAC colored tapes in centimeters (cm), while weight-for-height/length *z*-score and weight of children will be assessed in grams (g) with minimal and light clothing using UNISCALE, and height will be measured using a standard measuring tape in cm(s) and then will be compared with the grading of *z*-score chart. All the anthropometric measures will be taken thrice to reduce information bias. Additionally, all the instruments that will be used for taking measurements will be checked for accuracy and zero precision beforehand. All eligible participants will be recruited following a pre-defined inclusion and exclusion criteria (Table 1).

**Table 1 Tab1:** Inclusion and exclusion criteria

*Inclusion criteria*	*Exclusion criteria*
Ages 6–59 months at enrolment	
Acute malnutrition without complications, as defined by the WHO (i.e., children with MUAC < 115 mm or weight-for-height *z*-score < − 3 or grade 1–2 bilateral edema who will be clinically well and alert with good appetite	Presence of any complications of severe malnutrition (severe dehydration, severe anemia, severe pitting edema, anorexia, hypothermia, high pyrexia, acute lower respiratory infection, or hypoglycemia) or immune compromised
Parental consent for the child to participate	Declined parental consent
Healthy children without any chronic or acute illness	Children on antibiotic treatment for any disease in the last 3 months

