### Outcome parameters

All the assessments will be carried out by a trained staff unrelated to the enrolment and allocation procedures. The primary outcome of the trial is to examine the microbiome diversity of malnourished children, to compare it with healthy children, and to evaluate the effect of RUTF plus prebiotics on the microbiome diversity of malnourished children (Table 3). For achieving the primary outcome, 5 g stool sample of the children will be collected for DNA extraction using QIAamp DNA Stool kit (Qiagen, Hilden, Germany) for examining the microbiome diversity through 16 Svedberg (S) ribosomal ribonucleic acid gene sequencing.

**Table 3 Tab3:** Primary outcome parameter

*Outcome measure*	*Measure description*	*Time frame*
Microbiome diversity	Microbiome diversity examination among malnourished children using 16 Svedberg (S) ribosomal ribonucleic acid gene sequencing. The microbiome diversity index measures the diversity of microbial species in malnourished children’s gut microbiota, comparing it to reference and control populations. Higher values indicate greater diversity, providing insights into malnutrition’s impact on gut microbiota composition	8 weeks

For the accomplishment of secondary outcome parameters, anthropometric measures of the children, including their height, weight (for calculating weight-for-height/length z-score), and MUAC will be assessed by a trained healthcare staff. For assessing neurodevelopment of children, the Malawi Development Assessment Tool (MDAT) will be used that is considered to be one of the most valid tools for assessing child development for ages 0–59 months measuring their motor, language, social, and cognitive development [29], while for assessing the muscle mass accumulation, Body Stat Analyzer will be used (Table 4).

**Table 4 Tab4:** Secondary outcome parameters

*Outcome measures*	*Measure description*	*Time frame*
Anthropometric measurements	Change in the mean weight-for-height/length *z*-score and MUAC in children with complicated severe acute malnutrition who have been taking prebiotics supplementation for 8 weeks	8 weeks
Neurodevelopment assessment	Impact assessment of prebiotic supplementation on children’s neurodevelopment using the Malawi Development Assessment Tool	8 weeks
Muscle mass accumulation	The study investigates the impact of prebiotic consumption on body composition changes using the Body Stat Analyzer as a quantitative measurement tool	8 weeks

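### Height is described as tape-measured and graded on a chart in one section and used to calculate a z-score in another; reconcile the two and replace the tape

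*Protocol article*

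**What the plan says.** The section on study population and eligibility criteria gives the measurement method. Weight "will be assessed in grams (g) with minimal and light clothing using UNISCALE". Then "height will be measured using a standard measuring tape in cm(s) and then will be compared with the grading of" a z-score chart. The same section adds safeguards: "All the anthropometric measures will be taken thrice to reduce information bias", and "all the instruments that will be used for taking measurements will be checked for accuracy and zero precision beforehand".

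Table 1 offers alternative entry routes: "Acute malnutrition without complications, as defined by the WHO (i.e., children with MUAC < 115 mm or weight-for-height" z-score below −3, or grade 1–2 bilateral edema.

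The section on outcome parameters describes the z-score differently: "height, weight (for calculating weight-for-height/length z-score), and MUAC will be assessed by a trained healthcare staff". Table 4 then lists the secondary endpoint as "Change in the mean weight-for-height/length" z-score and MUAC at 8 weeks. The statistical analysis section compares the three groups by ANOVA (or Kruskal–Wallis) and tests within-group change by paired t-test (or Wilcoxon). Table 5 places both eligibility screening and the baseline anthropometry at week 0.

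**The concern.** A mean change in z-score needs a continuous z-score at both visits. The eligibility section describes a comparison with a chart grade, which may return only a band. The outcome section speaks of a calculation but names no device, reference or method. Because screening and baseline fall in the same week, a value read at screening could easily become the baseline half of the change score.

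If that happened, recovery within a band would go unrecorded. If the chart has a single band below −3, a child moving from −4.5 to −3.1 would show no change, while one moving from −3.05 to −2.95 would show a full grade.

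The second issue is the instrument. Children are enrolled from 6 months and the endpoint is named for height or length, yet the stated device is a tape. A tape has no fixed head and foot reference, and averaging three readings reduces random error but not a systematic one. At stake are the precision of one secondary endpoint and the classification of children near the −3 cut-off.

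**Working it through.** **1. The plan's own figure.** The sample size section uses a balanced one-way ANOVA with k = 3, f = 0.25, alpha 5% and power 80%. The noncentrality is n·k·f² = 53 × 3 × 0.0625 = 9.94, which gives power 0.805 (n = 52 gives 0.797). So 53 per group is reproduced. It is not disputed here and serves only as the arm size below.

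**2. The passages side by side.**
- Eligibility section: tape, then comparison with a chart grade.
- Outcome section: height and weight taken to calculate the z-score.
- Table 4 and statistical analysis section: mean change, ANOVA or paired t-test, which fits a continuous value.
- Table 5: screening and baseline measurement both at week 0.

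No sentence says which value is recorded for analysis.

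**3. What a graded outcome would cost, if it were used.** The documents give no SD, expected gain or chart bands for the z-score, so all of these are assumptions:
- 53 children in each malnourished arm, two-sided 5% t-test between the two arms.
- The standardized difference detectable with 80% power is 0.549. With an SD of change of 0.8, this is 0.549 × 0.8 = 0.44 z.
- Baseline z normal with mean −3.6 or −3.3 and SD 0.5 or 0.7, truncated below −3; comparator gain 0.5, 1.0 or 1.5.
- Bands 1 SD wide, with one open band below −3.

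| Quantity | Exact z | Graded z |
|---|---|---|
| Arm difference | 0.44 | 0.29–0.43 |
| Power at 53 per arm | about 80% | 54–68% |
| Children needed, relative | 1 | 1.3–1.9 |

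The relative number is the squared ratio of standardized differences. In the worst case this is (0.550/0.401)² = 1.88.

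Table 1 also admits by MUAC or edema, so the calculation was repeated with only some children below −3. The further assumptions were a difference of 0.4 with SD 0.7 or 0.5 with SD 0.9, gain 0.5–1.5, baseline mean −3.6 and SD 0.5 for those below −3, and the others spread evenly from −3 to −2. Exact power is about 80–83%. Graded power is 63–70% with 70% of children below −3, and 66–70% with 50% below.

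**4. Length error.** If weight at a given z scales with length to the power p, and 1 z is a fraction c of weight, a 1 cm error at length L shifts the z-score by about (1/L) × p/c. Assume p = 1.8–3 and c = 0.08–0.10. At 70 cm:
- low: (1/70) × 1.8/0.10 = 0.26
- high: (1/70) × 3/0.08 = 0.54

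*Random error.* With error SD s per reading, shift h per cm and m readings averaged at each of two visits, the required n rises by the factor 1 + 2(s·h)²/(m × 0.8²). Assume s = 0.5–1.0 cm and h = 0.20–0.45.
- One reading: from 1 + 0.02/0.64 = 1.03 to 1 + 0.405/0.64 = 1.63.
- Mean of three independent readings: 1.01 to 1.21.

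*Systematic error.* A bias that is the same at both visits enters both z-scores almost equally and largely drops out of the change. Under blinding it also drops out of the contrast between the two malnourished arms. It does not drop out at a fixed cut-off, or if the child is measured lying at one visit and standing at the other.

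**The case against.** The chart sentence stands in a section about screening, while the outcome section says the z-score is calculated, and the planned analyses fit a calculated value. A reader might infer that the endpoint is coarse and floored at −3. The documents do not support that as a fact. Three points stand against it:
- The chart's bands are not described, so an open lowest band is an assumption.
- Table 1 admits children by MUAC or edema, so not every child starts below −3.
- A calculated z-score has no floor.

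A reader might also infer that grading harms eligibility. It does not: reading a child as above or below −3 from a chart loses nothing for that purpose, so only length error can matter there.

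On the tape, no document figure supports a 1 cm error. The plan also provides three readings, instrument checks, trained assessors separate from enrolment and allocation, and a 2-day training. These limit random error, and a stable bias largely cancels in the contrast of interest.

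Finally, an article may leave the measuring position, the combination of readings and the software to the full protocol, so their absence is not the point. What remains is what the article does state: a tape, a chart grade, and a different account of the z-score elsewhere.

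**Conclusion.** The point holds as a conditional one. The article gives two accounts of how the z-score is obtained and must settle on one. If the grade were the analysed value, power would fall from about 80% to roughly 54–70% under the assumed baseline distribution, gains, SDs and bands. If the z-score is calculated, there is no loss. The tape is a poor stated choice for children from 6 months. A 1 cm error would move the z-score by about 0.26–0.54 at 70 cm under the assumed scaling, with consequences mainly at the −3 cut-off or when position changes between visits. One secondary endpoint and one of the three entry routes are concerned. The primary outcome and the sample size are not. The change should be made because it is cheap and clearly better than the stated method.

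**What to change.** State once, for both eligibility and outcome, that the weight-for-height/length z-score is calculated as a continuous value from the WHO standard, using the mean of the three weight readings and the mean of the three length or height readings. Amend the eligibility section so that it agrees with the outcome section. Replace the tape with a length/height board, and measure each child in the same position at week 0 and week 8.

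The cost is one board at each of the two hospitals and brief instruction within the planned 2-day training. No extra visits, staff or participants are needed.
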